## Abstract

**Background:**

Poor adherence to inhaled medication may lead to inadequate symptom control in patients with respiratory disease. In practice it can be difficult to identify poor adherence. We designed an acoustic recording device, the INCA® (INhaler Compliance Assessment) device, which, when attached to an inhaler, identifies and records the time and technique of inhaler use, thereby providing objective longitudinal data on an individual’s adherence to inhaled medication. This study will test the hypothesis that providing objective, personalised, visual feedback on adherence to patients in combination with a tailored educational intervention in a community pharmacy setting, improves adherence more effectively than education alone.

**Methods/design:**

The study is a prospective, cluster randomised, parallel-group, multi-site study conducted over 6 months. The study is designed to compare current best practice in care (i.e. routine inhaler technique training) with the use of the INCA® device for respiratory patients in a community pharmacy setting. Pharmacies are the unit of randomisation and on enrolment to the study they will be allocated by the lead researcher to one of the three study groups (intervention, comparator or control groups) using a computer-generated list of random numbers. Given the nature of the intervention neither pharmacists nor participants can be blinded. The intervention group will receive feedback from the acoustic recording device on inhaler technique and adherence three times over a 6-month period along with inhaler technique training at each of these times. The comparator group will also receive training in inhaler use three times over the 6-month study period but no feedback on their habitual performance. The control group will receive usual care (i.e. the safe supply of medicines and advice on their use). The primary outcome is the rate of participant adherence to their inhaled medication, defined as the proportion of correctly taken doses of medication at the correct time relative to the prescribed interval. Secondary outcomes include exacerbation rates and quality of life measures. Differences in the timing and technique of inhaler use as altered by the interventions will also be assessed. Data will be analysed on an intention-to-treat and a per-protocol basis. Sample size has been calculated with reference to comparisons to be made between the intervention and comparator clusters and indicates 75 participants per cluster. With an estimated 10 % loss to follow-up we will be able to show a 20 % difference between the population means of the intervention and comparator groups with a power of 0.8. The Type I error probability associated with the test of the null hypothesis is 0.05.

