### Sample size calculation

Studies in the pharmacy setting have identified rates of baseline rates of attempted adherence amongst asthma patients of below 0.6 [12]. In the primary care setting poor inhaler technique amongst patients with respiratory disease has been identified in preliminary studies conducted using the INCA® device (47 %, standard deviation 33.0). A pre-intervention actual adherence rate of 0.5 at the end of the first month is, therefore, assumed. The primary endpoint is the rate of actual adherence at the end of the study period. A comparison between adherence rates in the intervention and comparator groups will be conducted at the end of months 1, 2 and 6. The sample size is thus dictated by comparisons to be made between these two groups.

It is hypothesised that the intervention group will get closer to the commonly reported level of ‘good’ adherence (≥0.8) [23] improving by 0.2. Adherence in the comparator group may improve as a result of the educational intervention received and an assumed improvement of 0.05 in this group over the study period has been incorporated into the sample size calculation. An intra-class correlation coefficient of 0.025 and a loss to follow-up of 10 % (as observed in a recent similar study conducted in the pharmacy setting [14]) are assumed. With a power of 0.85 at the 0.05 significance level to detect a 0.2 difference in actual adherence between the two groups, a sample size of 75 participants across 25 clusters in each of the intervention and comparator groups is required.

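### The abstract and the sample size section attach different powers (0.8 and 0.85) to the same 75 participants, and the abstract writes cluster where it means study group

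*Protocol article*

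**What the plan says.** The abstract (Methods/design) reports that the calculation "indicates 75 participants per cluster". It goes on to say that, for a gap of 20 % and with 10 % expected loss, the trial can show a "difference between the population means of the intervention and comparator groups with a power of 0.8", at a Type I error of 0.05.

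The section Sample size calculation assumes an intra-class correlation of 0.025 and 10 % loss to follow-up. Its power statement reads "With a power of 0.85 at the 0.05 significance level", and the target is again a gap of 0.2 in actual adherence. The size it derives from this is given as "a sample size of 75 participants across 25 clusters in each of the intervention and comparator groups is required".

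On the meaning of cluster, the abstract itself says "Pharmacies are the unit of randomisation", and Randomisation and allocation repeats this. The abstract also refers to "comparisons to be made between the intervention and comparator clusters", where the word can only mean the two study groups.

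**The concern.** The two places describe one calculation with the same headline inputs but report different powers, and the article does not reconcile them. A reader cannot tell which power the trial was designed for.

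In a cluster randomised trial the number of participants per cluster sets the design effect. Using the same word for a pharmacy and for a whole study group therefore obscures the figure on which the clustering adjustment depends. Power and sample size are the commitments against which the final result, and especially a null result, will be judged.

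**Working it through.** **Side by side**

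| Item | Abstract | Sample size calculation |
|---|---|---|
| Number | 75 per cluster | 75 per group, 25 pharmacies per group |
| Power | 0.8 | 0.85 |
| Difference | 20 % | 0.2 |
| Significance level | 0.05 | 0.05 |
| Loss to follow-up | 10 % | 10 % |

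**Step 1: can one number serve both powers?** For a comparison of two means, the required number is proportional to (z for alpha + z for power)², whatever the standard deviation (SD), difference, design effect or loss. Two-sided at 0.05:
- power 0.80: (1.960 + 0.842)² = 7.85
- power 0.85: (1.960 + 1.036)² = 8.98
- ratio: 8.98 / 7.85 = 1.14

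The requirement differs by about 14 %, so 75 cannot be the required number for both. This step needs no SD.

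**Step 2: unit.** 75 / 25 = 3 participants per pharmacy. Design effect = 1 + (3 − 1) × 0.025 = 1.05.

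**Step 3: trying to reproduce 75.** The article gives no SD for actual adherence. The only SD in the section is 33.0 (0.33), which belongs to preliminary data on poor inhaler technique. Using it for adherence is my assumption. The article does not say whether the test is one- or two-sided; two-sided is assumed first. The section also mentions a 0.05 gain in the comparator group. If that is subtracted from the 0.2 gain in the intervention group, the difference is 0.15, so both values are shown.

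n per group = 2 × (z sum)² × 0.33² / difference², rounded up, then × 1.05, then / 0.9:

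| Difference | Power | n | After design effect and loss |
|---|---|---|---|
| 0.20 | 0.80 | 43 | 51 |
| 0.20 | 0.85 | 49 | 58 |
| 0.15 | 0.80 | 76 | 89 |
| 0.15 | 0.85 | 87 | 102 |

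None gives 75. One-sided, the four final figures are 40, 47, 70 and 82. Treating adherence as a simple proportion gives 82 to 233 with all adjustments. Close values appear only when a stated adjustment is left out: 76 (two-sided, power 0.80, difference 0.15, no design effect and no loss) and 74 (one-sided, power 0.85, difference 0.15, design effect but no loss).

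**Step 4: power that 75 per group would give.** Effective number per group after loss = 75 × 0.9 / 1.05 = 64.3. Power = Φ[(difference / 0.33) × √(64.3 / 2) − 1.96]:
- difference 0.20: Φ(3.44 − 1.96) = about 0.93
- difference 0.15: Φ(2.58 − 1.96) = about 0.73

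Before loss the values are about 0.95 and 0.78.

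**Step 5: SD that the stated powers would need.** SD = difference × √(64.3 / 2) / (z sum):
- difference 0.20: 0.405 for power 0.80, 0.378 for power 0.85
- difference 0.15: 0.304 for power 0.80, 0.284 for power 0.85

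The conclusion of steps 3 and 4 therefore moves with the assumed SD. That of step 1 does not.

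**The case against.** **Before and after loss.** The best defence of the two powers is that 0.85 applies before loss and 0.8 after it. The arithmetic allows this: (1.960 + 1.036) × √0.9 = 2.84, and Φ(2.84 − 1.96) is about 0.81. The abstract does mention the 10 % loss in the sentence that gives 0.8. However, the Sample size calculation section lists the same 10 % among its assumptions just before it states 0.85, and the Discussion says that loss has been allowed for in the sample size. The text does not support this reading, though it could explain how the mismatch arose.

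**A 25-fold difference in size.** A reader might combine 75 per cluster with 25 clusters and infer 1,875 participants per group. The documents do not support this. The abstract gives no number of clusters, and its own sentence uses clusters for the two groups. The Sample size calculation section states the design in full as 75 per group. Fifty pharmacies also fit within the 67 that remain after 10 of the 77 go to control. The planned size is not in dispute; only the word is wrong.

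**The SD.** It is fair to object that 0.33 is not given as the SD of actual adherence. A reader might infer that the stated SD disproves both powers. It does not, because the article states no SD for the primary outcome. The recalculation is conditional on that assumption.

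**Practical effect.** Choosing 0.8 or 0.85 alters nothing in recruitment, allocation or analysis. That stands, and it limits the weight of the point.

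**Conclusion.** The point holds as an inconsistency in stated design figures. The same 75 participants, 10 % loss, 0.05 level and 0.2 difference are given power 0.8 in one place and 0.85 in the other, so at least one is wrong as written. The gap corresponds to about 14 % in required number. The documents do not show which power was intended.

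The abstract's unit is a misuse of cluster for group. The operative figure is 75 per group across 25 pharmacies, about 3 each.

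Conditional on an adherence SD of 0.33, a two-sided test, a design effect of 1.05 and 10 % loss, neither power is reproduced: 75 per group gives about 0.93 for a difference of 0.20 and about 0.73 for 0.15. This is supporting evidence that the calculation should be restated, not proof that the trial is too small or too large.

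**What to change.** In the abstract, replace per cluster with per group (25 pharmacies per group, about 3 participants each), and use group wherever cluster means a study group.

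State one recomputed power in both places, with the difference (0.20, or 0.15 if the comparator gain is subtracted), the SD of actual adherence, the intra-class correlation, the attrition, and whether the test is one- or two-sided. If a power before loss and a power after loss are both meant, label each.

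The cost is a text correction and one recalculation, for which the sponsor must supply the SD it used. Enrolment and trial conduct do not change.

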**Discussion:**

This clinical trial will establish whether providing personalised feedback to individuals on their inhaler use improves adherence. It may also be possible to enhance the role of pharmacists in clinical care by identifying patients in whom alteration of either therapy or inhaler device is appropriate.

**Registration:**

ClinicalTrials.gov NCT02203266.

**Electronic supplementary material:**

The online version of this article (doi:10.1186/s13063-016-1362-9) contains supplementary material, which is available to authorized users.

## Background

Asthma and chronic obstructive pulmonary disease (COPD) are common, chronic respiratory diseases [1, 2]. Both conditions are characterised by symptoms such as wheeze, breathlessness and airflow limitation [3, 4] which vary in intensity from patient to patient.

Appropriate pharmacological treatment, used correctly, can help to reduce symptoms and improve quality of life [3, 4]. Inhaled medications are commonly prescribed but can be difficult to use and this can lead to technique errors [5, 6] that may have both direct costs such as medication waste, and indirect costs such as increased use of other health care resources as a consequence of poor symptom control [7].

Community pharmacist-delivered interventions have been shown to improve inhaler technique [8, 9], inhaled mediation adherence rates [10] and therapeutic outcomes [11–14] for adult patients with asthma [8, 9, 11–14] and COPD [8, 10]. However, adherence rates in reported studies are frequently either based on patient self-report which has been shown to be unreliable [15, 16] or calculated from pharmacy databases containing prescription refill data which provide information on medication obtained but not on how such medication is used in practice [17, 18].

We developed a device, INCA®(INhaler Compliance Assessment), which makes a digital acoustic recording of an inhaler being used [19]. In this study the device is attached to a salmeterol/fluticasone Diskus® (Seretide Diskus®, also known as Seretide Accuhaler®) inhaler. When a patient opens their Diskus® inhaler (by sliding a thumbgrip to expose the mouthpiece) the INCA® device switches on and begins to audio record. The recordings are analysed using automated signal processing techniques, thus providing an objective assessment of both time and technique of inhaler use [19].

Participants’ adherence to their inhaled medication will be described in terms of both attempted and actual adherence rates. Where the participant opens their Diskus® inhaler, initiating an audio recording, this is classed as an attempt to take the inhaled medication. The pattern of attempts over a defined period will provide an ‘attempted’ rate of adherence. Analysis of the associated acoustic recordings allows for detection of correct inhaler technique, which we take to indicate that the participant actually received the dose they attempted to take. Thus, the pattern of attempted doses with correct technique yields the ‘actual’ rate of adherence.

We hypothesise that the INCA® device, when used as part of a community pharmacist-delivered adherence-focussed educational consultation, can support medication management in patients with respiratory disease.

## Methods

### Study setting

This is a prospective, cluster randomised, parallel-group, multi-site study comparing two pharmacist-delivered strategies to optimise inhaler technique and adherence in respiratory patients in the community setting. The study will be conducted in a chain of 77 community pharmacies operating in the Republic of Ireland. Pharmacies are eligible for inclusion in the study if they have patients who are prescribed a salmeterol/fluticasone Diskus® inhaler and if those patients have regularly attended the pharmacy to collect a prescription in the 6 months prior to enrolment. The study period is from 2014 with ongoing recruitment.

### Participants

Adult patients of both sexes aged 18 years or older who use, or are capable of using, a salmeterol/fluticasone Diskus® inhaler and are in possession of a current valid prescription for the same, are eligible to enrol on the study.

### Inclusion and exclusion criteria

In order to meet inclusion criteria for the study patients must be capable of understanding, and willing to provide, voluntary informed consent before any protocol-specific procedures are performed; be capable of understanding and complying with the requirements of the study protocol; demonstrate a willingness to attend for all required visits; be able and willing to use inhaled medication and have a history of regular attendance at the pharmacy in which they are recruited, receiving at least three prescriptions for any medication filled in the prior 6 months .

Patients are excluded from the study if they have a known sensitivity to salmeterol/fluticasone, if their physician has indicated that they will not be continuing to receive salmeterol/fluticasone Diskus® over the 6-month study period or if they have used any investigational product or device within the 3 months prior to enrolment.

### Study design

A cluster randomised study has been chosen in order to minimise the risk of contamination of knowledge by the pharmacists across the three study groups. The study flow is indicated in Fig. 1 (see Additional file 1).

**Fig. 1 Fig1:**
[figure not shown]
INCA® Pharmacy Study – overview of study flow and design

Patients identified in the community pharmacy, who meet the inclusion and do not violate the exclusion criteria, will be invited to participate in the study and are provided with information about the trial in the form of a participant information leaflet. On enrolment, consent will be obtained and recorded. All study visits are conducted by a registered pharmacist.

At the initial visit each participant’s age, sex, dose of salmeterol/fluticasone, duration of taking this dose and details of concomitant medications will be recorded on paper-based case report forms which have been developed specifically for this study and piloted in a sample of three pharmacies. The pharmacist will record the Peak Expiratory Flow Rate (PEFR) as measured by an electronic peak flow meter (eMini-Wright®, Clement Clarke International, Harlow, England). The St. George’s Respiratory Questionnaire (SGRQ) [20], a validated tool used to assess quality of life in patients with diseases causing airway obstruction, will be completed by the participant. A history of inhaled therapy (salmeterol/fluticasone and short-acting beta agonists), steroid and antibiotic usage over the prior 6 months will be obtained from the participant’s patient medication record in the pharmacy. Participants will be asked to identify an aspect of their life affected by their respiratory condition that they would like to improve. This ‘breathing-related goal’ will be recorded and improvement will be monitored through the study period. The purpose of this is to provide an additional focus for the participant via which a tangible and personalised measure of any symptom improvement can be noted. Patient reported clinical diagnosis (asthma or COPD), smoking status and health pay status will also be recorded for all participants.

The participants will receive a salmeterol/fluticasone Diskus® inhaler with an INCA® device attached for use twice per day as prescribed. This inhaler will be provided free of charge to all participants, regardless of their health pay status, with the relevant professional service being paid by the patient in the usual manner. For all participants, the INCA® device is used to capture data on adherence and inhaler technique. Participants in the intervention and comparator groups will be asked to record their peak expiratory flow with the eMini-Wright® electronic monitor twice daily. In the intervention and comparator groups participants are also provided with a paper-based diary for recording daily symptoms, medication usage and health care utilisation. This diary, based on the Asthma Society of Ireland’s peak flow diary [21], has been developed specifically for this study and piloted in a sample of seven patients. An extract of the diary is provided in Fig. 2 (see Additional file 1).

**Fig. 2 Fig2:**
[figure not shown]
Extract of participant respiratory diary

After the initial visit (visit 1), follow-up visits are scheduled 30 (visit 2), 60 (visit 3), 150 (visit 4) and 180 (visit 5) days later. At visits 2, 3 and 5 the participants return their inhalers with the INCA® devices. Visit 4 is a dispensing visit. At each of these visits, for control group participants, changes in medications (including new medications) are recorded as is progress towards the participant’s ‘breathing-related goal’. For intervention and comparator group participants this information is also noted along with the SGRQ responses. Assessment of inhaler technique, using an inhaler technique checklist and inhaler technique training based on assessment observations, is given to both intervention and comparator participants.

### Interventions

#### Intervention group: feedback using recordings from the INCA® device

Participants in the intervention group will receive the INCA® intervention. These participants will receive feedback on their own inhaler use, with personalised information on their technique and timing of use of the salmeterol/fluticasone Diskus® inhaler as recorded on the INCA® device at day 30 (visit 2), day 60 (visit 3) and day 180 (visit 5). Utilising a structured review, the pharmacist will aim to identify barriers to good adherence and support patients to improve habit of use where necessary. Remediation of errors of inhaler use identified through assessment of participants’ inhaler technique using a Diskus® inhaler technique checklist, the ‘Inhaler Proficiency Schedule’ (IPS) [22], will also be conducted.

### Comparator group: inhaler technique education

The comparator for this study is current best practice in the community pharmacy setting, defined for this study as an assessment of the participant’s inhaler technique using a Diskus® inhaler technique checklist (IPS) [22] and a physical demonstration of optimal technique by the pharmacist followed by demonstration of the same by the participant until device mastery is achieved.

### Control group: usual care

In order to control for trial participation effects a control group is included the study design. Participants in the control group will receive no intervention other than usual care (i.e. the safe supply of medicines and advice on their use). Review of inhaler technique, as initiated by the pharmacist where deemed necessary, or as requested by the participant, is a feature of usual care but its provision is not a standard or structured intervention in the control group.

Upon exiting from the study at visit 5, all participants will receive personalised feedback on their Diskus® use based on the INCA® device recordings.

### Objectives

The objective of this study is to assess whether providing personalised feedback on adherence and technique errors will lead to better adherence and clinical outcomes for participants than current best practice.

### Primary outcome

The primary study objective is to determine whether there is at least a 20 % greater rate of actual adherence in the INCA® feedback group (‘intervention group’) compared to the current best practice group (‘comparator group’) post intervention. Thus, the primary outcome measure will be the rate of participant adherence to their inhaled medication, defined as the proportion of correctly taken drugs at the correct time relative to the prescribed interval (defined for this study as the dosing interval ±25 %). To accommodate for potential Hawthorne effect comparisons of the rate of actual adherence at 2 months and at 6 months will be performed.

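### The primary objective asks for an advantage of at least 20%, but the trial is sized as an ordinary superiority test with 0.2 as its design difference, and the assumed improvements imply 0.15

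*Protocol article*

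**What the plan says.** The protocol article describes the aim of the primary comparison in four places.

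- **Objectives:** personalised feedback is assessed for whether it "will lead to better adherence and clinical outcomes for participants than current best practice". No threshold is given.
- **Primary outcome:** "The primary study objective is to determine whether there is at least a 20"% greater rate of actual adherence in the intervention group than in the comparator group. This sentence does not say whether the 20% is absolute or relative.
- **Abstract, Methods/design:** the trial is said to be able to show a 20% "difference between the population means of the intervention and comparator groups with a power of 0.8", and "The Type I error probability associated with the test of the null hypothesis is 0.05". The value of the null is not written out.
- **Sample size calculation:** the trial is sized "With a power of 0.85 at the 0.05 significance level to detect a 0.2 difference in actual adherence between the two groups". The planning values behind this are: "A pre-intervention actual adherence rate of 0.5 at the end of the first month is, therefore, assumed"; the intervention group is expected to move towards good adherence, "improving by 0.2"; and for the comparator group "an assumed improvement of 0.05 in this group over the study period has been incorporated into the sample size calculation".

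Statistical methods plans a multilevel model for the primary analysis and names neither a margin nor a non-zero null. It defers detail to a statistical analysis plan, which is not shown.

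**The concern.** Read as written, the objective is a threshold question. To conclude that the advantage is at least 20 points, the data must exclude smaller advantages, so the lower confidence limit has to lie above 0.20. A trial powered to detect 0.2 does something else: it is likely to exclude zero if the truth is 0.2. The same number is thus the bar to clear in one section and the assumed truth in another.

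The primary objective governs what the trial may claim. Left as it is, a result that is significant against no difference could be presented as meeting an objective it does not support. Equally, a real benefit of 0.15, which is what the assumed improvements amount to, could be called a failure.

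**Working it through.** **Inputs.** From Sample size calculation: difference 0.2, power 0.85, significance level 0.05, intra-class correlation 0.025, 10% loss to follow-up, 75 participants in 25 clusters per group (3 per cluster). The only SD given is 33.0, for preliminary inhaler-technique data; using 0.33 for actual adherence is an assumption. Two-sided testing is also an assumption.

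**The plan's own figure.** n per group = 2 × [SD × (1.96 + 1.036) / difference]².

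- Difference 0.2: 2 × [0.33 × 2.996 / 0.2]² = 48.9. Times the design effect 1 + 2 × 0.025 = 1.05 gives 51.3; divided by 0.90 gives 57. The stated 75 is not reproduced.
- Difference 0.15: 86.9, then 91.3, then 101.4, so 102. The stated 75 is not reproduced here either.

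Because 75 does not follow from the stated inputs, I use two standard errors (SE) for the between-group difference.

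- **SE A, from SD 0.33.** Evaluable per group 75 × 0.90 = 67.5, or 2.7 per cluster; design effect 1 + 1.7 × 0.025 = 1.0425; effective size 67.5 / 1.0425 = 64.7. SE = 0.33 × √(2 / 64.7) = 0.058.
- **SE B, from the stated power.** Power 0.85 at 0.2 implies SE = 0.2 / (1.96 + 1.036) = 0.067, which corresponds to an SD of about 0.38.

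**Smallest significant observed difference (against zero).** 1.96 × SE = 0.114 (A) or 0.131 (B). Both are well short of 0.20.

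**Chance of showing the threshold.** P(lower 95% limit > 0.20) = Φ[(d − 0.20) / SE − 1.96], where d is the true difference. For comparison, P(significant against zero) = Φ[d / SE − 1.96].

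| True difference d | Significant vs zero, A | Significant vs zero, B | Lower limit > 0.20, A | Lower limit > 0.20, B |
|---|---|---|---|---|
| 0.15 | 0.73 | 0.61 | 0.002 | 0.003 |
| 0.20 | 0.93 | 0.85 | 0.025 | 0.025 |
| 0.25 | 0.99 | 0.96 | 0.14 | 0.11 |
| 0.30 | >0.99 | 0.99 | 0.41 | 0.32 |
| 0.35 | >0.99 | >0.99 | 0.73 | 0.61 |

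For an 80% chance, d = 0.20 + 2.80 × SE = 0.36 (A) or 0.39 (B).

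**Which null is meant?** At d = 0.20 the chance of rejecting a null of 0.20 in favour of the intervention is 2.5% whatever the SE. The protocol claims 0.85 (0.8 in the Abstract) at that same difference. A null of 0.20 is therefore incompatible with the stated power, and a null of zero is the only natural reading.

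**Implied difference.** Intervention 0.50 + 0.20 = 0.70; comparator 0.50 + 0.05 = 0.55; difference 0.15. The same section states 0.2.

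**Scale.** On an absolute reading, 0.15 falls short of 0.20. On a relative reading, 0.70 / 0.55 = 1.27, a 27% advantage, which passes; the threshold would then be 0.55 × 1.2 = 0.66, an absolute difference of 0.11.

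**The case against.** The best defence is that the threshold is a target difference loosely worded into an objective. The Objectives section asks only for better adherence, no section mentions a margin, and nothing says that p < 0.05 will be reported as proof of a 20-point gain. As a reading of intent this is probably right. It does not help the sentence in Primary outcome, which states the threshold as what the trial is to determine.

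Several stronger readings are tempting and should be resisted.

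- A reader might infer that the objective cannot be met or answered. The planned model can give an estimate and confidence interval to set against 20%, and a very large true effect would probably show it.
- A reader might take a null of zero as stated. It is not written anywhere; it is inferred from the power statement.
- A reader might say the protocol expects 0.15 and so makes its own objective false. The between-group difference it states is 0.2. The 0.15 is arithmetic on its assumed improvements, in a paragraph that says the comparator's 0.05 was incorporated. That is an internal contradiction, not a declared expectation.
- A reader might say that 0.70 against 0.55 fails the objective outright. That holds only on the absolute scale. The Abstract and the Sample size calculation point that way, but Primary outcome does not say so.

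It is also fair to object that the SD of 0.33 belongs to technique data, and that baseline adjustment could lower the SE. The figures are therefore given as a range; the conclusion is the same at both ends.

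**Conclusion.** The point stands as a misalignment of objective, implied test and planning difference. A significant primary result, possible from an observed difference of about 0.11 to 0.13, would not show an absolute advantage of at least 20 points. Even if the true difference were exactly the 0.2 used for sizing, the chance of showing the threshold would be 2.5%; at 0.15 it is 0.2% to 0.3%. Separately, 0.15 and 0.2 cannot both be the planning difference. If it is 0.15, the power of 75 per group is about 0.73 (SD 0.33) or 0.61 (SE implied by the stated power), not 0.85.

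This rests on two-sided testing, an inferred null of zero, the absolute scale, and either the borrowed SD or the stated power. The 2.5% depends on neither of the last two. The endpoint, model and data collection are not in question.

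**What to change.** In Primary outcome, replace the threshold sentence with: *to test whether mean actual adherence at month 6 differs between the intervention and comparator groups (null hypothesis of no difference, two-sided 0.05), and to estimate the absolute difference with a 95% confidence interval*. Delete the requirement of at least 20% greater adherence.

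In Sample size calculation, label the planning difference as a design assumption in absolute percentage points, not a success criterion. Reconcile 0.15 with 0.2 and restate the power for whichever is kept.

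If the threshold is truly intended, the alternative is to define a non-zero null on a stated scale and re-size the trial for it.

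The cost of the main fix is a few sentences. The claim becomes less ambitious, and if 0.15 is the planning difference, the stated power falls or the sample size must rise (about 102 per group for 0.85 power with SD 0.33).
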